#### Privacy and Confidentiality

After logging into the French Gut registration site, participants will be assigned a pseudonym that will be created using the anonymization or pseudonymization techniques recommended by the National Agency for the Security of Information Systems and the French Data Protection Authority (CNIL). This pseudonym is guaranteed to be nonidentifiable. The reference is unique and will be retained for the entire duration of the study. Furthermore, the results will be reported only in aggregate form and not on an individual basis.

#### Compensation Details

Participants will be kept informed about the progress of the study and its overall results through regular newsletters, shared on participants’ accounts, as well as through webinars exclusively dedicated for them. Participation in this research is voluntary and does not offer any possibility of personal benefit, nor does it entitle participants to any compensation, except the one mentioned above.

### Participant Journey

To take part, volunteers need to answer a 53-item online questionnaire about their health, lifestyle, and dietary habits, and collect a compliant stool sample. The participant’s journey is detailed in Figure 1.

#### Registration and Questionnaire

To take part in the study, volunteers need to create a personal account on the project’s website [29]. Registration and data collection take place directly on the project website, using an end-to-end encrypted connection. The questionnaire and data are stored in an HDS-certified environment (SKEZIA), provided by a company specializing in eHealth solutions and e-cohorts. The entire platform was initially developed and tested in a development environment before being deployed in production and made accessible to participants. After checking that the volunteer is eligible and has signed the informed consent form, the volunteer completes the questionnaire, which consists of 53 items divided into 3 different parts (Multimedia Appendix 3). The first part of the questionnaire provides sociodemographic data (duration of residence in mainland France, mode of delivery, etc) as well as lifestyle data (smoking habits, sedentary lifestyle, and physical activity). The second part of the questionnaire provides information on anthropometric characteristics (weight and height) used to calculate the BMI. This section also collects health data, including chronic diseases. In order to characterize the digestive health of the volunteers, the questionnaire also includes questions relating to gastrointestinal symptoms and factors influencing digestive health. This questionnaire also includes the Bristol Stool Consistency Scale [32]. It also contains questions to define an assessment of a participant’s mental well-being called the “Perceived Stress Scale 4” or PSS-4 [33]. The third part of the questionnaire is devoted to the dietary habits. First, food exclusions and specific types of diet are addressed. The volunteers then indicate, for each of the food families present in the questionnaire, the frequency of their usual daily or weekly consumption. In addition, the questionnaire focuses on the specific dietary factors that have an impact on the gut microbiota. Overall, the 53 questions are distributed across 4 web pages. These questionnaires are adaptive, and each page contains an average of 16 questions (ie, the request for clarification on certain items only appears if the participant answered “yes” to the first question, for example, to provide a specific digestive disease). Full completion of the questionnaire is mandatory to move on to the next stage, that is, receiving the kit at home. Volunteers can modify their answers as long as they have not submitted the questionnaire. Once submitted, the participant can contact the investigation team at any time to indicate whether any of the eligibility criteria have changed (ie, antibiotics taken between completion of the questionnaire and sample collection), or to modify their responses after the submission of the questionnaire. The questionnaire is a one-shot and can only be completed once.

As the project progresses, additional questionnaires will be offered to participants who have agreed to be recontacted for further contribution to scientific explorations. These questionnaires will be more detailed on health, lifestyle, and dietary habits. They will not be mandatory, but they will help us to answer specific scientific questions that emerge as the project progresses.

The validity of the data is verified by input and consistency checks. The questionnaire database is stored in an HDS environment and the metagenomic data on the MGP’s information technology infrastructure, as close as possible to the sequencing instruments and the heavy bioinformatics processing.

#### Stool Sampling

After completing the initial questionnaire, a stool sampling kit is sent to the volunteer. The stool sample is collected at home by the volunteer in a tube containing a stabilizing liquid buffer (DNA and RNA shield). The date and time on which the sample was taken is handwritten by the volunteer on the pouch containing the tube. After sampling, the tube is mailed directly to the investigation team via a prepaid envelope. The investigation team checks the conformity of the sample (eg, presence of identification data on tube, missing sample, and broken tube). Samples that do not pass the initial quality control are flagged up and a new sampling is scheduled. Quality control–validated samples are stored at –80 °C at the MGP-SAMBO BRC (Biological Resources Center), which is ISO 9001–certified and labelled GIS-IBiSA (CRB N°242), until further processing.

### Stool Sample Processing

#### DNA Extraction and Shotgun Sequencing

Total fecal DNA will be extracted using an in-house automated protocol that has been developed and improved on the International Human Microbiome Standards (IHMS) standard procedures (SOP 07 [34]). Extracted DNA is evaluated by fluorometric quantification, purity assessment, and fragment size analysis, then if suitable, sequenced using a high-throughput short-read DNA sequencer. A minimum of 2×20 million paired-end reads of 150 nucleotides is produced for each sample.

#### Microbial Gene Abundance Table and Taxonomical Profiling

Sequencing data are cleaned to (1) remove remaining sequencing adapters, (2) trim low-quality reads, and (3) discard reads too short (<60 bp) using Alien Trimmer (v0.4.0) or equivalent quality trimming software [35]. Reads mapping to the human genome are removed using Bowtie2 (v2.5.4) [36]. Microbial gene abundance and taxonomical profiling are then performed using Meteor2 [37] with our up-to-date gene microbial genes [30] and species (clustered with MSPminer [38]) catalogs of the human microbiota. Gene abundance profiling table is generated by mapping the reads onto the genes catalog. Species abundances are estimated as the mean abundance of the species marker genes. Richness and diversity parameters are computed using the species abundance table with Vegan R package [39]. Our catalogs will be continuously updated throughout the project based on newly identified clustered species, newly available taxonomy, gene annotations, and genomes.

### Contribution of the SNDS

The French national health data system also referred to as SNDS contains individual data for all reimbursements of health expenses for more than 99% of residents of French territory, that is, more than 65 million people. This system enables powerful analyses both in terms of the number of subjects involved and the hindsight now available (data collected since 2007). Available data are both administrative and medical. Administrative data are mainly sociodemographic data (age, sex, complementary universal health cover [named CMU-c], etc). Medical data include, among others, the list of chronic diseases of the volunteers that are 100% reimbursed by the French medical system or, for example, the exhaustive list of reimbursed drugs that have been prescribed over the years. Collecting the social security number during inclusion allows direct matching between the SNDS data and gut microbiota data from Le French Gut study.

This matching will allow us to gain a deep insight on the connection between the present participant’s health and its gut microbiota. It will also bring light on how the participant’s medical history is connected to its present gut microbiota profile.

### Statistical Methods

The statistical plan is designed to address both primary and secondary outcomes. It is structured into 6 distinct work packages, each targeting key aspects of the gut microbiome and its interactions.

First, microbial ecology and variability: this work package aims to characterize microbial ecology, variability, and composition across the French population. The main objective is to consolidate validated ecological tools and develop new ones leveraging the statistical power of this study. These tools will capture microbial variations at multiple levels, including alpha and beta diversity metrics, enterotypes [2], local partitioning [40], microbial guilds, and taxonomic ranks down to the strain level. These ecological tools will be analyzed across the entire French population. In addition, this work package will investigate how regional environmental exposures (air, water, soil, etc) correlate with microbiome variations.

Second, gut microbiome in healthy individuals: this work package focuses on establishing baseline profiles of the gut microbiome in healthy individuals. The first objective is to define and characterize a healthy population based on lifestyle habits, dietary patterns, and quality of life. Clustering techniques will be applied to classify individuals based on lifestyle factors (eg, smoking, alcohol consumption, and physical activity), dietary habits, and quality-of-life indicators (eg, sleep quality, digestive symptoms, and perceived stress). These clusters will allow us to explore whether the microbiome can reflect and influence the accumulation of risk factors in the healthy French population. The second objective is to assess the predictive potential of the microbiome for future health outcomes. Using the SNDS database, we will evaluate whether participants develop pathologies over a 10-year follow-up and identify microbiome signatures associated with disease onset.

Third, this work package investigates the relationship between the gut microbiome and the presence of pathological conditions. The pathological population will be characterized in terms of lifestyle habits, dietary patterns, and existing conditions. The project’s extensive statistical power will enable the stratification of pathologies, facilitating validation of known microbial signatures and identification of novel microbial markers linked to disease progression.

Fourth, this work package explores interactions between dietary patterns and microbiome composition. The first step involves characterizing dietary habits within the French population, both globally and with a focus on specific food components such as proteins, fibers, and polyphenols. We will then analyze how these dietary patterns influence and are influenced by the gut microbiome.

Fifth, this work package focuses on characterizing nonbacterial components and subdominant members of the microbiome. The large sample size will enable the exploration of less-studied gut ecological niches and microbes, including archaea, viruses, fungi, and protozoa. Their distribution, abundance, and associations with lifestyle, quality of life, and health conditions will be examined. In addition, we will investigate subdominant microbial species and strains that remain unexplored due to limited sample sizes in previous studies.

Sixth, this work package examines the influence of environmental exposures, including antibiotic and other medication use, on the microbiome. The first step involves stratifying the population based on medication and antibiotic usage. We will then assess microbiome responses to these exposures, with a specific focus on antibiotics. Thanks to the SNDS database, we will analyze antibiotic exposure data spanning the 20 years before participants’ enrollment (ie, up to 2006), allowing an in-depth investigation of the relationship between multiple antibiotic exposures and antibiotic resistance in the gut microbiome.

Given the explanatory nature of Le French Gut, each work package statistical plan will be further refined as data exploration progresses.

Each work package will use comparable statistical tools, methods, and analytical approaches. Except for work packages 1 and 5, the initial statistical step in each work package consists of characterizing the data collected from all included volunteers. Descriptive statistics (eg, mean and SD for continuous variables and contingency tables for categorical variables) will be used to summarize the data. Graphical visualizations, univariate analyses (eg, *t* tests and ANOVA), and multivariate analyses (eg, principal component analysis, factorial analysis for mixed data, and network analysis) will be performed to explore data structure, detect outliers, and identify potential stratifications.

For univariate analyses, conventional statistical tests (eg, Mann-Whitney-Wilcoxon, *t* test, Kruskal-Wallis, and chi-square tests) will be used to compare microbial, dietary, sociodemographic, and clinical variables across predefined volunteer groups. *P* values will be adjusted using the Benjamini-Hochberg procedure to control the false discovery rate. Correlation analyses will be conducted to examine associations between microbial species of interest and sociodemographic, lifestyle, environmental, nutritional, and clinical parameters.

Multivariate analyses will serve both descriptive and predictive purposes. Descriptive multivariate methods such as principal component analysis, factorial correspondence analysis, clustering, multidimensional scaling, and bacterial co-occurrence network analyses will be used to structure and synthesize the data. Specific complexity-reduction approaches include enterotype classification, which discretizes microbial heterogeneity into a limited number of states [2], and microbial guilds, which identify clusters of species with coabundance patterns across conditions. In addition, unsupervised clustering methods will be used to define microbiome-based subpopulations independently of phenotypic characteristics, allowing unbiased subgroup discovery.

For predictive modeling, supervised learning techniques such as discriminant analysis, random forests, and regression models will be applied to assess the microbiome’s ability to predict phenotypes of interest, including disease presence, nutritional profiles, environmental exposures, and health trajectories. These models will be trained and validated using independent test subsets to evaluate their predictive performance.

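### The correlation analysis named for environmental parameters makes no allowance for regional exposures being shared within an area, so unless area is modelled, chance differences between areas may be declared as associations

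*Protocol article*

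**What the plan says.** All the relevant text is in the Statistical Methods section of the protocol article.

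- **Aim.** Under work package 1, "this work package will investigate how regional environmental exposures (air, water, soil, etc) correlate with microbiome variations". The article does not define the regions or say how an exposure is assigned to a participant.
- **Scope of the methods.** "Each work package will use comparable statistical tools, methods, and analytical approaches", so the methods that follow apply to work package 1.
- **Method for environmental parameters.** "Correlation analyses will be conducted to examine associations between microbial species of interest and sociodemographic, lifestyle, environmental, nutritional, and clinical parameters".
- **Group tests.** A list of standard tests, given as examples, ends with "Kruskal-Wallis, and chi-square tests) will be used to compare microbial, dietary, sociodemographic, and clinical variables across predefined volunteer groups". Environmental variables are not among those named there.
- **Multiplicity.** The p "values will be adjusted using the Benjamini-Hochberg procedure to control the false discovery rate".
- **Prediction.** Supervised models are to predict several phenotypes, environmental exposures among them. "These models will be trained and validated using independent test subsets to evaluate their predictive performance".
- **Status of the plan.** "each work package statistical plan will be further refined as data exploration progresses".

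The section names no area-level analysis, random area effect, cluster-robust variance or spatial method. Regression is mentioned only for predictive modelling.

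**The concern.** An air, water or soil exposure assigned by region takes at most as many values as there are regions. For that question the area is the independent unit and participants are clustered within it. A participant-level correlation takes its standard error from the number of people. If microbiomes differ between areas for any reason unrelated to the exposure, that variation enters the estimate but not the standard error, and the p value is too small. This needs no confounding: it happens when exposure and area differences are unrelated.

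Benjamini-Hochberg assumes valid input p values, so it cannot correct this. Adding participants within the same areas makes it worse, because each area grows while the number of areas does not. At stake is a list of species declared associated with a regional exposure, many of which could reflect only which areas happened to differ.

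Prediction has a parallel problem, but only where the target is assigned by area. If the test subset is drawn by person, the same areas appear in training and test data, and a model that merely recognises the area can look as if it predicts the exposure.

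**Working it through.** **Figure in the plan.** The article gives no power, precision or error figure for regional exposures, so there is none to reproduce. The power statement under Sample Size concerns enterotype B2 and diseases of interest.

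**Inputs from the article.** Planned N = 100,000 (Study Design); 20,000 enrolled by January 2025 (Results); more than 2,500 species (Sample Size), taken as 2,500.

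**Assumed inputs.** Number of areas J = 13, 96 or 1,000, plus 10,000 as a very fine grid. ICC of a species' abundance within area from 0 to 0.01. Two-sided 5% tests, equal area sizes, false discovery rate level 5%.

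**Formulas.** For an exposure constant within areas of size m = N/J:

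- design effect: DEFF = 1 + (m − 1) × ICC
- true error of a nominal 5% participant-level test: 2 × [1 − Φ(1.96/√DEFF)]

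**Example.** N = 100,000, J = 13, ICC = 0.001: m = 7,692; DEFF = 1 + 7,691 × 0.001 = 8.69; 1.96/√8.69 = 0.665; error = 0.506. The effective sample size is 100,000/8.69, about 11,500.

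**True error at N = 100,000:**

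| Areas (m) | ICC 0 | ICC 0.0001 | ICC 0.001 | ICC 0.01 |
|---|---|---|---|---|
| 13 (7,692) | 0.050 | 0.141 | 0.506 | 0.824 |
| 96 (1,042) | 0.050 | 0.062 | 0.170 | 0.562 |
| 1,000 (100) | 0.050 | 0.051 | 0.062 | 0.165 |
| 10,000 (10) | 0.050 | 0.050 | 0.051 | 0.061 |

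**True error at N = 20,000.** With 13, 96 and 1,000 areas it is 0.219, 0.074 and 0.052 at ICC 0.001, and 0.628, 0.264 and 0.072 at ICC 0.01. Going from 20,000 to 100,000 participants in the same areas raises the error.

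**Simulation check.** 2,500 species with no true association, one shared exposure, equal areas, 20 runs per setting, for 13 and 96 areas. The participant-level error at N = 100,000 was 0.508 (13 areas) and 0.171 (96 areas) at ICC 0.001, and 0.825 and 0.561 at ICC 0.01, in agreement with the formula. After Benjamini-Hochberg, the mean number of falsely declared species was:

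| Areas | ICC 0 | ICC 0.0001 | ICC 0.001 | ICC 0.01 |
|---|---|---|---|---|
| 13 | 0.05 | 19 | 1,097 | 2,046 |
| 96 | 0 | 0 | 60 | 1,270 |

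**After the fix.** A test on area means with J − 2 degrees of freedom had a simulated error of 0.048 to 0.052 in every setting, at both sample sizes, with on average 0 to 0.2 false discoveries per 2,500 species.

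**The case against.** The strongest reply is that the error is inferred. The article never says participants will be analysed as independent; naming correlation does not by itself fix the unit of analysis; the work-package plans are to be refined; and a fuller plan, not shown, may already contain an area-level or multilevel analysis. This stands as a limit on the wording: the point is conditional. It does not remove the point, because the one method named for environmental parameters is, in standard form, unsuitable for an exposure shared within an area. The level at which an exposure is assigned is also a design fact that need not wait for data exploration.

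Four stronger readings are tempting and are not supported:

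- **That chance differences will be reported as exposure effects.** The article promises correlations, and the inflation runs from negligible to severe on two quantities it does not give. An ICC as high as 0.05 would give larger errors, but nothing in the article supports that as a central value. Kits go to home addresses, so a fine geographic unit is conceivable.
- **That the primary outcome is compromised.** That outcome is descriptive. Regional exposures are an additional aim of work package 1 and are not named among the primary or secondary outcomes.
- **That every test listed is at fault.** The group-test list consists of examples and does not name environmental variables; the point rests on the correlation sentence.
- **That all prediction of environmental exposures is affected.** Work package 6 counts medication and antibiotics as environmental exposures, and those are individual. The test-set point holds only for area-assigned targets, and only if subsets are split by person.

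It is also fair that a single random-intercept model may not suit every exposure: air, water and soil may follow different geographies, and neighbouring areas may be correlated. The fix therefore allows a spatial model.

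**Conclusion.** The point holds in conditional form. The method named for environmental parameters takes no account of exposures shared within areas, so unless area is modelled, p values for these exploratory associations may be much too small. With areas of about 1,000 to 7,700 participants, an ICC of only 0.001 is enough to raise a nominal 5% error to about 17% to 51%; at ICC 0.01 the range is about 56% to 82%. With 1,000 areas the figures are about 6% and 16.5%. With an ICC near zero, or about ten participants per area and an ICC up to 0.01, the error stays at about 5% to 6%.

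These figures rest on assumed ICCs and area counts and on equal area sizes. That Benjamini-Hochberg does not repair the problem does not depend on the exact values: whenever the input p values are materially too small, the adjusted ones are too. The change is worth making because it is cheap and improves on the stated method, though it concerns an exploratory aim.

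**What to change.** In Statistical Methods, for exposures assigned by area:

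1. State the geographic unit of each exposure.
2. Replace the participant-level correlation with an analysis that accounts for that unit: an area random intercept or a spatial model, or area means where areas are few. Base degrees of freedom on the number of areas.
3. Apply Benjamini-Hochberg to the resulting p values.
4. Where a predictive model targets an area-assigned exposure, hold out whole areas as the test subset. Individual exposures such as medication do not need this.
5. State that precision for these exploratory associations depends on the number of areas, and not only on the number of participants.

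The cost is a change of wording and a little more analysis work. No new data are needed beyond the area of residence already required to assign the exposure. The downside is wider intervals and fewer declared associations for regional exposures.

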### Sample Size

The sample size was calculated taking into account the main objective, which is to specify the presence and the abundance of over 2500 microbial species of the digestive tract and, in particular, the number of subjects required to characterize the enterotype B2 [3]. The enterotype B2 is a fairly rare ecological configuration of the microbiota that is most frequently associated with low-grade inflammation, higher prevalence of cardiometabolic conditions, and predictive of nonresponse to a diet designed to promote weight loss. According to a power test performed on French fecal samples from the MetaCardis cohort, with a population of 100,000 individuals and an expected prevalence of enterotype B2 of 5%, we will have the statistical power needed to characterize 74% of the microbiome that makes up the enterotype B2 with an α risk of 0.05 and β risk 0.80. A total of 100,000 participants will provide sufficient statistical power to assess the link between the composition of the gut microbiota and diseases of interest, but also to assess the composition of the intestinal microbiota of asymptomatic individuals at high risk of developing a disease. Indeed, diseases of interest include type 2 diabetes (prevalence of 6.4% in 2022), heart disease (8.3%), long-term psychiatric disease (4.1%) but cancer (2.3%) [31].

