## Results

Recruitment started in September 2022. As of January 2025, we enrolled 20,000 participants. The first scientific publications based on the data analysis are expected by mid-2025.

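### Microbiome associations are assigned to unadjusted tests and correlations, so at the planned size confounded differences can pass the false-discovery filter

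*Protocol article*

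**What the plan says.** The Statistical Methods section of the protocol article gives each class of method a role, and says that all work packages will use comparable tools.

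- **Group comparisons.** Conventional tests, labelled univariate, "will be used to compare microbial, dietary, sociodemographic, and clinical variables across predefined volunteer groups". Their P values are adjusted by Benjamini-Hochberg at an unstated level.
- **Associations.** "Correlation analyses will be conducted to examine associations between microbial species of interest and sociodemographic, lifestyle, environmental, nutritional, and clinical parameters". No partial or adjusted form is named, and the text does not say whether the Benjamini-Hochberg step covers them.
- **Multivariate methods.** These serve description (ordination, clustering, networks) or prediction. Regression appears once, among the supervised-learning tools used to predict phenotypes from the microbiome.
- **Stratification.** Work package 3 stratifies pathologies, and work package 6 stratifies by medication and antibiotic use. The initial descriptive step looks for further possible strata. None of these names age, sex, BMI or stool consistency.

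The relevant covariates are available. Registration and Questionnaire lists smoking, physical activity, weight and height, the Bristol scale and diet. Contribution of the SNDS lists age, sex and reimbursed drugs.

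On direction, work package 4 states: "We will then analyze how these dietary patterns influence and are influenced by the gut microbiome". Work package 2 likewise speaks of the microbiome influencing the build-up of risk factors.

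**The concern.** People with and without a disease, or with different diets, can be expected to differ in age, sex, BMI, lifestyle and drugs, and each of these may be related to the abundance of gut species. An unadjusted test cannot tell a difference due to the disease from one due to such a factor. Benjamini-Hochberg does not help, because a confounded difference is a real difference between the groups compared. It is attributed to the wrong cause, but it does not arise by chance.

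Sample size makes this worse. The Sample Size section says: "A total of 100,000 participants will provide sufficient statistical power to assess the link between the composition of the gut microbiota and diseases of interest". The same power detects very small confounded differences. At stake are the secondary outcomes on diet, lifestyle and disease, and the disease signatures and markers that work packages 2 and 3 set out to find. A separate risk is that a cross-sectional association between diet and microbiome is reported as influence in a stated direction.

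**Working it through.** **The plan's own figure.** The Sample Size section says that 74% of the enterotype B2 microbiome can be characterised. This cannot be recomputed, because the species-level effect sizes and variances are not given. The detectable standardised difference can be derived as (z for two-sided α + z for power) × sqrt(1/n1 + 1/n0). The article prints "with an α risk of 0.05 and β risk 0.80"; I read this as power 0.80, since taken literally it would mean 20% power. The stricter level is 0.05/2,500 = 0.00002.

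| Group at N = 100,000 | n1 vs n0 | Detectable at 0.05 | Detectable at 0.00002 |
|---|---|---|---|
| Enterotype B2 (5%) | 5,000 vs 95,000 | 0.041 SD | 0.074 SD |
| Type 2 diabetes (6.4%) | 6,400 vs 93,600 | 0.036 SD | 0.066 SD |
| Cancer (2.3%) | 2,300 vs 97,700 | 0.059 SD | 0.108 SD |

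**Inputs for the confounding check.**
- From the article: a target of 100,000 participants; "As of January 2025, we enrolled 20,000 participants"; type 2 diabetes prevalence of 6.4%; and "the presence and the abundance of over 2500 microbial species of the digestive tract", taken as 2,500.
- Assumed: the group gap D in one confounder (in SD), the within-group correlation r between confounder and species, 500 species linked to the confounder, independent species, no true disease effect, and a Benjamini-Hochberg level of 0.05.

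**One species.** The induced difference is D × r.
- At N = 100,000, SE = sqrt(1/6,400 + 1/93,600) = 0.0129 SD.
- At N = 20,000, SE = sqrt(1/1,280 + 1/18,720) = 0.0289 SD.
- For D = 1 and r = 0.05 (or D = 0.5 and r = 0.1) the induced difference is 0.05 SD. At N = 100,000, z = 0.05/0.0129 = 3.87, and the test rejects with probability 97% at 0.05.

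**All species.** Benjamini-Hochberg was applied to 2,500 unadjusted tests, with 200 simulations per scenario.

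| Induced difference (D × r) | z, N = 100,000 | Mean species declared | z, N = 20,000 | Mean species declared |
|---|---|---|---|---|
| 0.0125 SD (0.25 × 0.05) | 0.97 | 0.6 | 0.43 | 0.1 |
| 0.025 SD (0.25 × 0.1 or 0.5 × 0.05) | 1.93 | 43 | 0.87 | 0.4 |
| 0.05 SD (0.5 × 0.1 or 1 × 0.05) | 3.87 | 468 | 1.73 | 17 to 18 |
| 0.10 SD (1 × 0.1) | 7.74 | 521 | 3.46 | 413 |

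The last count at N = 100,000 agrees with a hand check. If all 500 linked species pass, the chance share is 0.05 × 2,000/2,500 = 4%, and 500/(1 − 0.04) = 521.

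**With adjustment.** If the confounder is removed correctly, about 0.03 to 0.10 species are declared on average, and any false finding occurs in 2.5% to 8% of runs (nominal 5%). An individual-level check at N = 100,000 with D = 0.5 and r = 0.1 was run 60 times. The unadjusted Mann-Whitney test rejected at 0.05 in 58 of 60 runs, and regression with the confounder as covariate in 1 of 60.

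**Direction of influence.** The core questionnaire can be completed only once (Registration and Questionnaire). A second stool sample is described only when the first fails quality control (Stool Sampling). Later questionnaires are optional. The core data therefore show diet and microbiome at one time, and none of the named methods separates the two directions.

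**The case against.** The strongest reply is that this is a journal article. The full protocol and any analysis plan are not shown, and covariate lists are commonly left to them. The method lists are open-ended, each work package plan is to be refined as exploration progresses, and nothing says that adjustment will not be done. A reader might infer that the study will never adjust; the article does not support that. What remains is that it goes beyond omitting detail. It gives group tests, correlations, multivariate methods and regression their purposes, and in that division adjusted estimation of associations has no place. Refinement during exploration is also not a prespecified confounder set.

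Other objections stand in part:

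- A reader might infer that confounded signatures are certain. They are not: with a weak confounder (0.0125 SD) almost nothing passes, and at the 20,000 participants reported so far the counts are much smaller.
- Some stratification is planned, and the Discussion says that firm conclusions need further research. This softens the problem but does not deal with age, sex, BMI or lifestyle.
- A reader might infer that each person gives only one questionnaire over the whole study. Study Design foresees follow-up with additional ones, so later diet could be related to the first sample. They are optional and the study stays observational, so the causal wording is still too strong.
- One covariate list for every analysis would be wrong. Drugs are the exposure in work package 6, and BMI and stool consistency may be mediators.

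**Conclusion.** The point holds in limited form and should be acted on. As written, the named association analyses are unadjusted although the main confounders are available, and false-discovery control does not protect against confounding. At the planned size the consequence ranges from under one to about 520 of 2,500 species per disease comparison, and at 20,000 participants from about 0.1 to 413. The range depends on the assumed confounder strengths and on the assumed 500 linked species, neither of which the documents give. The near-complete correction under adjustment assumes a confounder that is measured and modelled correctly; residual confounding would leave more. The wording on influence goes beyond what the core design can show. The documents do not support the conclusion that confounded signatures will necessarily be reported, or that adjusted models are absent from the full protocol or analysis plan.

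**What to change.** - Make the main association analysis a regression for each species and for diversity, adjusted at least for age and sex.
- Choose further covariates per work package from those collected: BMI, smoking, Bristol score, diet, reimbursed drugs, and processing batch if it is recorded, which the article does not say. Do not adjust for the exposure under study, for example drugs in work package 6.
- Show models with and without possible mediators such as BMI and stool consistency.
- Apply Benjamini-Hochberg to the adjusted P values, report effect sizes with intervals, and keep the univariate tests as description.
- In work packages 2 and 4, replace the language of influence with the language of association.

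The cost is plan wording, code and some extra analysis. No new data collection is needed for the covariates named in the article. Fewer species may be reported as signatures. The change should be settled before signatures are published.
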